## Abstract

**Background:**

A significant number of patients who undergo a standard inguinal hernia repair or a Pfannenstiel incision develop chronic (> 3 months) post-surgical inguinal pain (PSIP) due to nerve entrapment. If medication or peripheral nerve blocks fail, surgery including neurectomies may offer relief. However, some patients do not respond to any of the currently available remedial treatment modalities.

Targeted spinal cord stimulation (SCS) of the dorsal root ganglion (DRG) is a relatively new type of therapy that has a potential to significantly reduce chronic PSIP. The Axium® SCS System (Spinal Modulation Inc., NY, USA) has been shown to be safe and successful in small cohorts of PSIP patients.

Aim of this study is to evaluate targeted spinal cord stimulation therapy in patients with PSIP.

**Methods:**

A prospective, multicentre, randomized controlled trial with optional one-way crossover will assess the efficacy of the Axium® SCS system for the treatment of PSIP. Seventy-eight patients with intractable PSIP following open hernia repair or Pfannenstiel incision who did not respond favorably to previous pain treatment regimens including a neurectomy will be randomized to either an Axium® SCS arm or a control arm receiving only conventional medical management (CMM).

Primary outcome is the difference in percentage of subjects with ≥50% pain relief after 6 months using a Numerical Pain Rating Scale (NPRS). Data are collected using a daily pain/sleep diary and a number needed to treat (NNT) analysis is performed. Various secondary outcomes will be collected.

**Discussion:**

Targeted SCS stimulation of the DRG using the Axium® SCS system will possibly offer significant pain reduction in patients with PSIP who are refractory to other treatment modalities.

**Trial registration:**

The study protocol is registered at the NIH Clinical Trials Registry (http://clinicaltrials.gov, ClinicalTrials.gov identifier: NCT02349659) on January 29, 2015.

## Background

Herniorrhaphies are performed 800.000 times a year in the U.S. A male person in the industrialized world faces an up to 27% lifetime risk of requiring surgery for his inguinal hernia [1]. Some 10–12% of these patients were found to report moderate to severe chronic pain after the operation [2–4]. Chronic postherniorrhapy inguinal pain may be caused by nociceptive, inflammatory or neuropathic changes, the latter depending on whether inguinal nerves are affected. A comparably related pain syndrome may occur after nerve entrapment following a lower abdominal pfannenstiel incision [5]. Both pain entities are also referred to as chronic post-surgical inguinal pain (PSIP) syndromes.

Recently, a consensus was proposed concerning the management of chronic postherniorrhapy inguinal pain [6]. If non-surgical options failed, a triple neurectomy with inguinal nerves removal via an inguinal approach is suggested. Success rates range from 50 to 100%, depending on surgical technique (open or laparoscopic) and definitions of outcome measures [7–9]. However, the suggested consensus did not address alternative treatment options once a patient was an all options non-responder. Interestingly, a recent study showed that the number needed to harm, defined as patients who had an increase > 25% of pain compared to preoperatively, was 1 of 8 patients at a 3 year follow up when a selective neurectomy accompanied by mesh removal was performed. [10]

Currently, few therapeutic options are available for patients demonstrating limited (or no) success after neurectomy. A promising new treatment tool is spinal cord stimulation (SCS) of the dorsal root ganglion. This novel variant of traditional SCS is claimed to effectively target the groin and has proved to be a safe and efficaous therapy in small, heterogeneous case series of patients with PSIP [11, 12]. In order to evaluate whether this therapy is an effective treatment option for PSIP, a randomized clinical trial comparing SCS to conventional medical management is proposed. [13] Aim of the present article is to report on characteristics regarding the set-up of this randomized clinical trial.

## Methods

### Study design

The SMASHING (Spinal Modulation After failed Surgery for chronic pain following Hernia treatment in INGuinal area) trial is a randomized, cross-over, multicenter study. The protocol is approved by the Regional Ethics Committee of the Máxima Medical Center, Veldhoven, The Netherlands (no. 1435). The objective is to evaluate the efficacy of SCS of the DRG with an Axium® SCS System of Spinal Modulation Inc. in patients with post-surgical pain after a hernia repair or pfannenstiel incision who did not favorably respond to a neurectomy. Clinical results of the Axium arm are compared with those in a CMM arm. Patient enrolment has started in February, 2015. The study protocol is registered at the NIH Clinical Trials Registry (http://clinicaltrial.gov, ClinicalTrials.gov identifier: NCT02349659).

### Inclusion criteria

Adults (18 years or older) of either gender suffering from persistent inguinal pain (minimum duration of 6 months) following either open or laparoscopic inguinal hernia repair surgery or a Pfannenstiel incision who have subsequently undergone and failed to respond to a neurectomy procedure will be considered for inclusion. Failure to benefit from additional treatment options such as peripheral nerve blocks, physical therapy, minimally invasive interventional pain procedures and medical regimens with at least a tricyclic antidepressant or similar neuropathic pain agents is required. Patients should have a minimum daily average baseline pain rating of 5 out of 10 in the inguinal area on an 11-point NPRS. Patients should be able to operate the device. Inclusion criteria as set out by the Dutch Neuromodulation Society should be met. A psychologist will screen patients and assess for suitability within a multidisciplinary team including an anesthesiologist or pain specialist and a surgeon-herniologist. [6]

Patients are excluded if there are contra-indications for device implantation such as pregnancy, ongoing infection, coagulation disorders, previous spinal surgery at or between vertebral levels T10-L2, the presence of other active implantable devices or a condition which will require MRI investigations. Patients are not allowed to undergo injection therapy or radiofrequency treatment at the target neural structure in the 3 months prior to inclusion. An escalating or changing pain condition and a diagnosis of cancer in the past 2 years are also considered as exclusion criteria.

### Randomization

Patients are considered for the trial if all criteria are satisfied. After suitability within is confirmed by the multidisciplinary team, informed consent is signed after patient is adequately informed and has agreed upon participation. Patients will be randomized in a 1:1 ratio to either arm. An independent statistician will generate and hold the allocation sequence, concealed from those involved in assessing eligibility and recruiting subjects.

### Interventions

The SCS group (Axium® Group, Fig. 1) receives an Axium® SCS System within 4 weeks after randomization. Implantation is performed in one of the participating centers by an experienced anesthesiologist or neurosurgeon. Electrodes are placed in the epidural space near the targeted DRG under sedation in a surgical theatre, using a transforaminal, fluoroscopy checked approach. During the procedure, the patient is asked if paresthesia elicited by stimulation covers the painful area. If so, electrodes are connected to an external stimulator if a trial phase is deemed needed. After a successful trial (defined as reaching adequate pain relief upon stimulation), a fully implantable device will be placed in a second session some 2–3 weeks later on as earlier suggested. [11, 12] After implantation, patient will be subjected to a standard follow-up schedule as dictated by the implanting center plus additional trial visits if needed.

**Fig. 1 Fig1:**
[figure not shown]
Basic design and follow-up schedule. Seven analysis groups are indicated (‘AG’) to refer to groups at several time points

After randomization, the CMM (CMM group, Fig. 1) will continue with prior pain treatments as previously initiated by their general practitioner or pain specialist. This regimen will generally comprise physical therapy and medications such as a tricyclic antidepressant (amitriptyline) and/or anticonvulsants (pregabalin, gabapentin, valproic acid), opioids or other analgesics, as is the standard protocol for neuropathic pain. Use and adjustment of pain medication is allowed and monitored. There are no restrictions to dosage and sort of pain medication including opioids.

However, interventional pain techniques are not allowed during this time period. If (pulsed) radiofrequency, epidural or peripheral injection or infusion therapy with analgesic agents or any other form of neurostimulation (traditional SCS, Deep Brain Stimulation, TENS) are performed, these treatments are considered as a protocol violation. After 6 months, patients will be offered to cross-over to the Axium ® Group. They will then receive treatment and follow-up as previously described.

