### Collection of data and clinical follow-up

Patients of both groups will undergo a follow-up visit after 2 weeks, 1 month, 3 months, 6 months and 12 months postrandomisation. Standardized questionnaires investigating quality of life, physical impairment, health resources utilization, subject satisfaction and adverse events will be completed. Validated questionnaires such as the EQ-5D, BPI, NPSI (Neuropathic Pain Symptoms Inventory) and a 7 point Likert Scale will be used. Pain and sleep will be evaluated using a pain-sleep interference diary containing an NPRS and DSIS over a 7-day period. Measures of average, worst and least pain during the previous 24 h are obtained using this diary. Primary analysis is conducted on average pain intensity scores. Physical examination will be performed in order to assess changes in neuropathic pain symptoms.

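### The ban on interventional co-treatments and TENS reads as a rule for the CMM arm only, so the unblinded 6-month comparison can shift somewhat towards Axium; state it for both arms.

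*Protocol article*

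**What the plan says.** All references are to the protocol article.

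- **CMM arm (Interventions, text after the Fig. 1 legend).** These patients "will continue with prior pain treatments as previously initiated by their general practitioner or pain specialist". Medication may be adjusted without limit on type or dose. A new paragraph then states: "However, interventional pain techniques are not allowed during this time period". It lists radiofrequency and epidural or peripheral injection or infusion, and adds "any other form of neurostimulation (traditional SCS, Deep Brain Stimulation, TENS) are performed, these treatments are considered as a protocol violation". The same paragraph goes on to offer cross-over to Axium after 6 months.
- **Axium arm (Interventions).** Implantation and trial stimulation are described. On later care the text says only: "After implantation, patient will be subjected to a standard follow-up schedule as dictated by the implanting center plus additional trial visits if needed". No co-treatment is excluded.
- **Entry (Inclusion criteria).** "Patients are not allowed to undergo injection therapy or radiofrequency treatment at the target neural structure in the 3 months prior to inclusion". Also excluded is "the presence of other active implantable devices". Neither rule reaches TENS. Patients need a "minimum daily average baseline pain rating of 5 out of 10" and must already have failed nerve blocks, minimally invasive interventional procedures and medication.
- **Endpoint (Collection of data; Study endpoints; Statistical analysis).** Pain is taken from a "pain-sleep interference diary containing an NPRS and DSIS over a 7-day period". The primary outcome is a reduction of at least 50% at 6 months, by intention to treat. The change from baseline is also compared by ANCOVA.

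**The concern.** A restriction on co-treatment protects a comparison only if it binds both arms. Here a rule with named techniques and a stated consequence is placed in the text on one arm. Two differences between the arms can follow, both after randomisation.

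1. **Added treatment in Axium.** A patient with poor relief from the device could receive an injection or radiofrequency before month 6 without breaking any stated rule. The same step in CMM is a violation.
2. **Withdrawn treatment in CMM.** A patient who uses TENS during the baseline diary and is allocated to CMM must stop it or become a violator, although CMM is described as continuing prior treatment. If TENS still helped, pain at 6 months is compared with a baseline recorded under treatment. An identical Axium patient has no stated duty to stop.

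Randomisation balances TENS use at baseline, but the rule acts afterwards, so neither randomisation nor baseline adjustment removes its effect. Intention to treat keeps patients in their arms but does not equalise what they receive. The Discussion rules out a placebo control, so blinding gives no protection to a self-reported outcome.

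**Working it through.** **Step 1: which arm does the ban cover?** The order of the text is CMM regimen, ban, CMM cross-over at 6 months. The period in the ban is therefore most naturally the CMM control period. The Axium paragraph, which comes earlier, contains no equivalent.

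**Step 2: do the entry criteria close the gap?**

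| Treatment | Before inclusion, all patients | CMM to month 6 | Axium to month 6 |
|---|---|---|---|
| Injection or radiofrequency at target | barred for 3 months | violation | no rule stated |
| Other implanted stimulators | excluded | violation | no rule stated |
| TENS | no rule stated | violation | no rule stated |

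The entry criteria do not govern follow-up, and they leave TENS open at baseline.

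**Step 3: the plan's own figures.** Inputs from Sample size: 50% against 10%, two-sided 0.05, power 90%, normal approximation with continuity correction.

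- Uncorrected: (1.96 × √(2 × 0.3 × 0.7) + 1.2816 × √(0.5 × 0.5 + 0.1 × 0.9))² / 0.4² = 25.4, so 26 per arm.
- Corrected: (25.44/4) × (1 + √(1 + 4/(25.44 × 0.4)))² = 30.2, so 31 per arm, as stated.
- Attrition: 62/0.8 = 77.5, so 78, as stated.
- Standard error of the planned difference: √((0.5 × 0.5 + 0.1 × 0.9)/31) = 0.105, or 10.5 points.

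**Step 4: possible size on the responder scale.** The article gives no use rates, so every range here is an assumption.

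- *CMM withdrawal.* A share f of 5% to 30% uses TENS or a non-implanted infusion at baseline, and stopping removes half or all (r = 0.5 or 1) of their 10% response chance. Shift = f × r × 10%, from 0.05 × 0.5 × 10 = 0.25 points to 0.30 × 1 × 10 = 3 points. With f at 5% to 20% and r = 1 it is 0.5 to 2 points.
- *Axium addition.* A share g of 5% to 30% of Axium non-responders (half the arm) receives a treatment barred in CMM, and a share q of 10% to 50% of these become responders. Shift = 50% × g × q, from 50 × 0.05 × 0.1 = 0.25 points to 50 × 0.30 × 0.5 = 7.5 points.

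The upper end of the second route is unlikely, because entry requires failure of nerve blocks and interventional procedures.

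**Step 5: possible size on the change score (CMM withdrawal only).** With f of 5% to 20% and d of 0.5 to 2 NPRS points still relieved, and no compensation by medication, shift = f × d: 0.05 × 0.5 = 0.025; 0.10 × 1 = 0.10; 0.20 × 2 = 0.40. With an assumed residual SD of 1.5, the standard error is 1.5 × √(2/31) = 0.38, so the central case is 0.10/0.38 = 0.26 of a standard error.

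**Step 6: effect on a false positive.** If the true rate were 10% in both arms, an exact calculation for the pooled z-test with 31 per arm gives a 2.8% chance of a significant result favouring Axium. A 1-point shift, split equally between the arms, raises it to 3.7%, and a 2-point shift to 4.8%.

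**The case against.** **A condensed article may omit a common rule.** The full protocol, or the neuromodulation-society criteria that patients must meet, may regulate co-treatment and TENS in both arms. This stands as a limit. But the article does state a rule, and in one arm. That differs from leaving a detail to another document, and if a common rule exists the correction is one of wording.

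**The wording may be meant for the whole trial.** The ban opens its own paragraph, and barring other neurostimulation makes most sense if the study device is the reference. This has some force. A reader might infer that Axium patients are expressly free to receive these treatments. The article does not say so. It is silent on them, and CMM-only is the more natural reading, not the only possible one.

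**The direction is not certain.** Unrestricted medication is also stated only for CMM, so a patient who stops TENS can escalate analgesics. This may offset part of the shift.

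**Few patients would be affected.** The continued CMM regimen is described as physical therapy and medication, without TENS, and entry selects patients who failed other options. Systemic infusion is a marginal case too, since the ban most naturally means epidural or peripheral infusion. This supports a small effect, not a zero one.

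**It would be visible.** Health resources utilization is collected at each follow-up visit and could show co-treatment. That helps interpretation but does not prevent the imbalance.

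**Conclusion.** The point holds as a minor one. The ban most naturally binds CMM alone, nothing comparable is stated for Axium, and both resulting routes favour Axium in an unblinded comparison.

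The size is unknown because it rests wholly on assumed use rates. It is probably small: even the extreme assumed value for either route, 3 or 7.5 points, lies below one standard error of 10.5 and far below the planned 40.

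Two stronger conclusions are tempting and not supported. One is that the shift could account for the planned effect or undermine the sample size. The ranges above do not reach that, and 31 per arm and 78 in total reproduce exactly. The other is that the lack of a TENS wash-out is an error in itself, so that TENS has to be stopped before the baseline diary. What matters is that both arms follow the same TENS rule, and keeping it stable serves as well as stopping it.

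**What to change.** 1. State that the ban, with the study device as the only exception, applies to both arms from randomisation to the 6-month visit.
2. Record any breach in the same way in both arms.
3. For TENS, set one rule for both arms: either stopped before the baseline diary or kept stable to 6 months. The choice is the sponsor's.

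This takes a few sentences by amendment, with no change to sample size or analysis. The costs are these:

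- The Axium arm becomes slightly more restrictive than routine care.
- The Update section reports 18 patients enrolled by November 2016. An amendment cannot correct their baselines or past follow-up, so it reduces the shift for the trial as a whole and does not remove it.
- Stopping TENS before the diary could lift some patients over the entry threshold of 5. With assumed untreated pain of mean 7 and SD 1.2, the share of users moving from below to above it is 5.8%, 15.5% or 45.2% for d = 0.5, 1 or 2. Multiplied by f = 5%, 10% or 20%, that is 0.3%, 1.5% or 9.0% of otherwise comparable patients, equally in both arms. Keeping TENS stable avoids this.

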### Collection of data and clinical follow-up

Patients of both groups will undergo a follow-up visit after 2 weeks, 1 month, 3 months, 6 months and 12 months postrandomisation. Standardized questionnaires investigating quality of life, physical impairment, health resources utilization, subject satisfaction and adverse events will be completed. Validated questionnaires such as the EQ-5D, BPI, NPSI (Neuropathic Pain Symptoms Inventory) and a 7 point Likert Scale will be used. Pain and sleep will be evaluated using a pain-sleep interference diary containing an NPRS and DSIS over a 7-day period. Measures of average, worst and least pain during the previous 24 h are obtained using this diary. Primary analysis is conducted on average pain intensity scores. Physical examination will be performed in order to assess changes in neuropathic pain symptoms.

### Study endpoints

The primary outcome is percentage of subjects experiencing a minimal 50% reduction in average daily pain intensity as measured using the average NPRS as noted in pain diaries in the Axium® group as compared to the CMM group. Group differences in the change in pain intensity scores (NPRS) at the 6-month FU visit are also calculated. The analysis will be done following an Intention to Treat (ITT) principle.

Secondary outcomes are an ‘as treated’ analysis of the percentage of subjects experiencing a minimal 50% reduction in average daily pain intensity (NPRS) at 6 months and the mean difference in the change in pain intensity scores (NPRS) between the successfully trialed subjects with the Axium® arm as opposed to the CMM arm. This ‘as treated’ analysis is important as it reflects clinical convention i.e. utilization of a therapy trial (TNS) to improve changes of a successful outcome with the fully implantable system. A number needed to treat (NNT) analysis at the 6-months time point for ≥30% and ≥50% pain relief is also performed. However, reduction in pain intensity is not the only clinically relevant outcome in chronic pain patients. Changes in disability, pain interference, neuropathic pain symptoms, sleeping disorders and health resources utilization are also investigated using validated questionnaires at baseline and each follow-up visit. (Fig. 2).

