### Statistical analysis

The primary analysis is a comparison of the proportion of responders (≥ 50% pain relief) in the Axium® versus CMM group at the 6-months time point. The mean difference between proportions and 95% confidence intervals are calculated. A risk difference is obtained using generalized linear modeling with a binomial distribution and an identity link. Difference between groups in the change in pain score (6-months minus baseline), adjusted for any chance imbalance between groups at baseline (ANCOVA model) are also calculated. The mean treatment effect (Axium® minus CMM) together with its 95% confidence interval is obtained. NNT will also be calculated as the reciprocal of the difference in proportions of responders (Axium® minus CMM) and presented with its 95% confidence interval. All analyses are conducted both ‘as randomized’ (intention to treat principle) and ‘as treated’ (secondary).

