## Discussion

The results of the presently proposed ´SMASHING´ trial may shed light on a possible viable alternative treatment option once other treatments have failed in therapy resistant patients with PSIP. A very recent consensus protocol does not address this group [6]. Based on a retrospective analysis of 10 CPIP patients who were implanted with DRG stimulation leads, the technique is very promising. Eight of these 10 patients reported > 50% pain relief whereas a 77% mean VAS reduction was attained. [11] However, it is obvious that a proper RCT is required using a cross-over design. Firstly, a placebo controlled setting is inappropriate as it is clearly noticeable for patients if a sham device is implanted because of the absence of paresthesia. Secondly, ethics direct that the control group is not to be denied access to the therapy for which a cross-over is offered. Thirdly, a control group is heterogeneous because of the often individually tailored treatments for these therapy-resistant patients. This heterogeneity however mirrors daily clinical practice, and therefore generalization of the forthcoming results will be realistic. Moreover, possible confounding variables are controlled with randomization. The PROCESS study used a similar construction [15].

It must be appreciated that the validation of various outcomes is of utmost importance in pain treatment studies. Pain reduction scores are subjective whereas the clinical relevance of a 30% or 50% pain reduction is debatable. The presently proposed outcome measurements are linked to improved patient satisfaction, diminished medication usage, daily functioning and sleeping quality and a positive expert’s opinion regarding patient’s improvement [16–19]. We will address these components as well as other secondary outcomes as all of these issues are indispensable for a thorough efficacy analysis of any type of novel pain treatment.

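### The as-treated comparison sets Axium patients selected after randomisation for early pain relief against the whole CMM arm, so its difference favours Axium and its NNT is too small for the treatment pathway

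*Protocol article*

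**What the plan says.** Study endpoints makes the ITT responder comparison at 6 months primary. It then adds, as secondary outcomes, an as-treated responder analysis and the mean difference in NPRS change "between the successfully trialed subjects with the Axium® arm as opposed to the CMM arm". It calls this analysis important because clinical practice uses a stimulation trial to raise the chance of a good outcome with the implant.

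Interventions fixes who qualifies: "After a successful trial (defined as reaching adequate pain relief upon stimulation), a fully implantable device will be placed in a second session". This happens after allocation, since the Axium group "receives an Axium® SCS System within 4 weeks after randomization". The trial phase is conditional: "electrodes are connected to an external stimulator if a trial phase is deemed needed".

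The CMM arm (Interventions, text after Fig. 1) has no corresponding step. Those patients "will continue with prior pain treatments as previously initiated by their general practitioner or pain specialist".

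Statistical analysis states that "NNT will also be calculated as the reciprocal of the difference in proportions of responders", and that all analyses are run both as randomised and as treated, the latter labelled secondary. The risk difference, the ANCOVA of NPRS change and the NNT therefore all have an as-treated version. The Discussion relies on the point that "possible confounding variables are controlled with randomization".

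**The concern.** Membership of the Axium side depends on an unblinded, early reading of pain relief, the same domain that is compared at 6 months. Patients who do not improve early drop out of that side. Their counterparts in the CMM arm cannot be identified and stay in. The two sides are then no longer exchangeable, and the protection that the Discussion claims from randomisation is given up. Baseline adjustment does not restore it, because the selection acts on something seen after baseline.

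The bias needs one condition: that early relief correlates with later relief. The plan's own reason for the analysis assumes exactly that.

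At stake are a secondary difference, its confidence interval and an NNT that the protocol presents as the clinically relevant result and nowhere labels non-randomised.

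**Working it through.** **Plan's own figures.** With 50% against 10%, 90% power and two-sided 5%, the normal approximation gives 25.4 per group, and 30.2 with the continuity correction, so 31. Then 62/0.8 = 77.5, so 78, or 39 per arm. Both stated figures reproduce. At these rates the ITT difference is 40 points and the NNT is 1/0.40 = 2.5.

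**Assumed inputs (not in the documents).** Share of the Axium arm passing the trial phase, s = 60-80%. SD of the 6-month NPRS change, 2.2 points. Correlation between early relief and 6-month change, ρ = 0.3-0.7. Every Axium patient is taken to have a trial phase.

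**No device effect, mean NPRS change.** If the best share s of the Axium arm on early relief is compared with all of CMM, then

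bias = SD × ρ × φ(z)/s, where z is the normal cut-off with share s above it.

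φ(z)/s is 0.644, 0.497 and 0.350 for s = 60%, 70% and 80%. Example: 2.2 × 0.5 × 0.497 = 0.55 points. False-positive rates come from simulation with bivariate-normal early relief and change and a two-sided pooled t-test, used here as a stand-in for the planned ANCOVA.

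**No device effect, responders.** With 10% true response in both arms, the same model gives the response rate among the selected patients. Its ceiling is 10%/s, reached if every responder passes the trial phase.

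| s | ρ | Bias in change (points) | False positives, 39 per arm | False positives, 31 per arm | Responder bias (percentage points) |
|---|---|---|---|---|---|
| 60% | 0.3 | 0.42 | 11% | 10% | 3.2 |
| 60% | 0.5 | 0.71 | 24% | 19% | 5.0 |
| 60% | 0.7 | 0.99 | 43% | 33% | about 6 |
| 70% | 0.3 | 0.33 | 9% | 8% | 2.3 |
| 70% | 0.5 | 0.55 | 17% | 14% | 3.5 |
| 70% | 0.7 | 0.76 | 31% | 24% | 4.1 |
| 80% | 0.3 | 0.23 | 7% | 7% | 1.5 |
| 80% | 0.5 | 0.38 | 12% | 10% | 2.2 |
| 80% | 0.7 | 0.54 | 19% | 15% | 2.5 |

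The responder ceilings are 10/0.6 − 10 = 6.7, 10/0.7 − 10 = 4.3 and 10/0.8 − 10 = 2.5 points. With ρ = 0 there is no bias. The ITT comparison stays at about 5%.

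**Planning rates, 50% against 10%.** Two simple cases for patients who fail the trial phase:

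- They never respond. The as-treated Axium rate is 0.5/s = 83%, 71%, 63% for s = 60%, 70%, 80%. The differences are 73, 61 and 53 points, and the NNT is 1.4, 1.6 and 1.9.
- They respond as CMM does. The rate is (0.5 − (1 − s) × 0.1)/s = 77%, 67%, 60%. The differences are 67, 57 and 50 points, and the NNT is 1.5, 1.75 and 2.0.

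A complier-average effect, the ITT difference divided by the share implanted, is 0.40/0.6 = 67, 0.40/0.7 = 57 and 0.40/0.8 = 50 points, identical to the second case. With less perfect sorting (ρ = 0.3-0.7, s = 70%) the as-treated difference is 46-55 points and the NNT 2.2-1.8.

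**What the NNT counts.** In the second case at s = 70%, 1.75 successfully trialed patients per extra responder correspond to 1.75/0.7 = 2.5 patients entering the pathway, which is the ITT figure.

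**The case against.** The analysis is labelled secondary, the primary analysis is ITT, and an ITT NNT is produced anyway. That stands: the primary conclusion cannot be altered by this set.

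A reader might infer that the shift from 40 to 50-73 points, and from an NNT of 2.5 to 1.4-2.0, is all bias. The arithmetic does not support this. A complier-average estimate from the randomised comparison gives 50-67 points over the same success rates, so most of the shift is a change of population, from all randomised patients to those who pass the trial phase.

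A reader might also infer that a useless device could appear to deliver the planned responder effect. It could not in expectation: at a 10% true rate the responder bias cannot exceed about 7 points at 60% success. The exposed measure is the mean NPRS change, and its highest error rates occur only at the strongest correlation with the lowest success rate.

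Nor does the article say that CMM patients with protocol violations remain in the as-treated set. It is silent on them, so nothing is built on that here. Because the trial phase is used only where judged necessary, selection would be weaker than modelled if few patients have one.

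What remains is that clinical convention justifies having a trial phase, not an unselected comparator for those who pass it. The ITT comparison already evaluates the pathway with its trial phase included.

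**Conclusion.** The concern holds for the secondary analysis. The as-treated difference is not a randomised comparison and leans towards Axium under the plan's own rationale. With no device effect, and under the assumed success rates, SD and correlations, the mean NPRS change is biased by about 0.2-1.0 points. The nominal 5% error becomes about 7-43% with 39 per arm or 7-33% with the planned 31. In the central case (ρ = 0.5, 70% success) it is about 17% and 14%.

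The responder bias is small against the planned 40 points: about 2-4 points at 70% success and at most 6-7 at 60%. The as-treated NNT is too small as a measure of the treatment pathway, because it omits patients who had electrodes placed and then failed the trial phase. At the planning rates that is mainly a matter of whom it counts rather than bias. The primary ITT analysis and the sample size are untouched.

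**What to change.** In Study endpoints and Statistical analysis:

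1. Calculate the NNT for ≥30% and ≥50% relief from the ITT difference only.
2. Report the responder rate and mean NPRS change of the successfully trialed patients descriptively, labelled non-randomised, with no between-arm test, confidence interval or NNT.
3. Optionally, if an effect in implanted patients is wanted, add a complier-average sensitivity estimate: the ITT difference divided by the proportion of the Axium arm permanently implanted, with a bootstrap interval. State its assumption that allocation does not affect 6-month pain in patients who are not implanted. Note that this may fail, because those patients have undergone electrode placement.

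The cost is wording in two sections and, if item 3 is used, one short computation; no new data or patients are needed. The downside is that the secondary result will look less favourable and loses its formal between-arm comparison.
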